### Participants

#### Teachers

One or two teachers from each enrolled school who teach students in grades 9 and 10 will be recruited to act as a ‘school champion’. They will attend a single full-day professional learning workshop delivered by members of the research team with tertiary qualifications in physical education (PE), health promotion, exercise physiology and/or strength and conditioning. School champions will receive curriculum materials and resources at the workshop and will be asked to deliver a separate 2-hour training for other grade 9 and 10 teachers at their schools, who also have the option to implement the programme with their classes. Teachers can deliver the RT4T sessions to their students during usual PE lessons, co-curricular school sport periods or within an elective subject known as Physical Activity and Sports Studies. Professional learning will align with the NSW Educational Standards Authority accreditation process. Lastly, the learning will contribute to teachers’ required annual training hours.^35 36^

#### Students

Secondary students in grades 9 and 10 (aged 14–16 years) enrolled in the study schools will be eligible to participate. The target population has been selected as this is the period during which students start to drop out of organised sport and can benefit from exposure to lifelong physical activities^37^ such as RT.

### Primary and secondary outcomes

A range of quantitative and qualitative methods will be used to assess primary and secondary outcomes at baseline (T0), 6-month (T1) and 18-month follow-up (T2). Our primary outcome is reach, operationalised as the proportion of grade 9 and 10 students from the study schools who participate in the RT4T programme. The proportion will be calculated as a percentage of students from grades 9 and 10 who participate in ≥50% of the RT4T practical sessions divided by the total number of students in grades 9 and 10 at the study schools. Secondary outcome measures include dose delivered, fidelity, sustainability, impact, cost-effectiveness and implementation determinants.

### Sample size calculation

We aim to recruit 90 secondary schools, with 30 schools assigned to each of the three treatment arms. This will include an estimated 261 classes and n=~7800 students across the three arms of the trial. Based on our previous research in secondary schools, we estimate 20% of schools will not provide usable data for our primary outcome at follow-up. As few studies have tested the effects of implementation strategies on the reach of the school-based physical activity interventions, there is little information to guide power calculations. Therefore, we estimated that the low support group will achieve 12.5% reach, while both the moderate and high support groups will achieve 25% reach (ie, between-group difference of 12.5%). Our power calculation is based on 90% power, type 1 error rate of 0.025 and SD of 12%. For the continuous secondary student effectiveness outcomes, we assumed an intraclass correlation coefficient estimate of 0.2. If 10% of schools provide usable data (~780 students), our study will have 80% power to detect significant small-to-moderate effects between the treatment arms.

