### Impact evaluation

Student-level outcome data will be collected from a convenience sample of students who provide informed parental consent. We anticipate that 10% of the sample will provide usable data (n~780 students). Fitness testing, participation in muscle strengthening activity and RT skill competency will be assessed using the RT4T app. The tablet version of the app (adapted from the ‘Burn 2 Learn’ programme)^57^ will be used by teachers to assess students’ fitness, student’s participation in muscle strengthening activity and RT skill competency. We will evaluate upper body muscular endurance using the 90° push-up test.^58^ Isometric abdominal muscular endurance will be measured using the plank hold test.^59^ Standing long jump will assess muscular power, 1 min sit to stand will assess lower body muscular endurance and the 10×5 m shuttle run will assess speed and agility. These fitness assessments are integrated into the RT4T programme and conducted by the teachers at the start (week 1) and at the end (week 8) of the 8-week intervention period.

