### Statistical analysis

Statistical analyses will be conducted by an independent statistical analysis service—Clinical Research Design, Information Technology and Statistical Support from Hunter Medical Research Institute. Analyses of the primary (programme reach) and secondary outcomes will be conducted using logistic mixed models (SAS Institute, Cary, North Carolina, USA) for dichotomous outcomes, and ordinal or linear mixed effects regression models for continuous outcomes. The primary outcome (ie, reach) will be collected at the school level and assessed using t-tests. Alpha levels will be set at p<0.025 for the comparisons of the moderate and high support arms against the low support arm. If the p values for the differences between the moderate and high support arms with the low support arm reach this threshold, the moderate and high support arms will be compared at a 5% significance threshold. For student-level outcomes, statistical analyses will be adjusted for the clustering of effects at the class level, as students from each school are nested in classes. Although clustering at the school level is negligible after adjusting for clustering at the class level, we will test this assumption and adjust our analyses for school-level clustering if required. For teacher-level outcomes, clustering will be accounted for at the school level. Two potential moderators of effects will be explored using interaction terms (ie, socioeconomic status of school and school location). School socioeconomic status will be determined using the Index of Community Socio-Educational Advantage (ICSEA), which will be obtained from the MySchool website.^60^ School ICSEA values are determined using student-level parent occupation and education data, school location (ie, remoteness), and percentage of indigenous student enrolment.

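### On the stated inputs, 80% power for the student outcomes is reached at about 0.64 to 0.70 SD, not at small-to-moderate effects

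*Protocol article*

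**What the plan says.** The Sample size calculation section sets the frame: "We aim to recruit 90 secondary schools, with 30 schools assigned to each of the three treatment arms". On numbers of classes and students it adds: "This will include an estimated 261 classes and n=~7800 students across the three arms of the trial". For the student outcomes it gives one further input, "For the continuous secondary student effectiveness outcomes, we assumed an intraclass correlation coefficient estimate of 0.2", and then the result: "If 10% of schools provide usable data (~780 students), our study will have 80% power to detect significant small-to-moderate effects between the treatment arms". It gives no numerical effect size, does not say whether the correlation applies to classes or schools, and states no correlation between baseline and follow-up.

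The Impact evaluation section reaches the same count in other words: "We anticipate that 10% of the sample will provide usable data (n~780 students". It describes recruitment as follows: "Student-level outcome data will be collected from a convenience sample of students who provide informed parental consent".

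The Statistical analysis section fixes two more inputs. On the error rate: "Alpha levels will be set at p<0.025 for the comparisons of the moderate and high support arms against the low support arm". On clustering: "For student-level outcomes, statistical analyses will be adjusted for the clustering of effects at the class level". It treats any remaining school-level clustering as negligible, subject to a test.

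**The concern.** The power statement is printed beside its inputs, so it can be checked. Nine schools supply only about 26 classes, and a correlation of 0.2 in classes of about 30 removes most of the information in 780 students. It is doubtful that what remains can detect a small-to-moderate difference between two arms.

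The sampling unit is a related difficulty. Whole schools and individually consenting students can give the same total of 780 but very different design effects, and the detectable difference depends heavily on which is meant.

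Effectiveness is one of the two aims of this hybrid trial. If a reader accepts the stated power, a null student-level result will look more informative about differences between the support models than it is.

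**Working it through.** **Inputs.** From the Sample size calculation section: 90 schools, 30 per arm; 261 classes; about 7800 students; ICC 0.2; 10% of schools, about 780 students; 80% power. From the Statistical analysis section: alpha 0.025 per comparison with low support, and adjustment for class. Alpha 0.05 is also shown because the student-level power statement names no alpha. My assumption: small-to-moderate means a standardised difference of about 0.2 to 0.5, since the article gives no number.

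**Cluster sizes.**
- Students per class: 7800/261 = 29.9
- Students per school: 7800/90 = 86.7
- Classes per school: 261/90 = 2.9
- Ten per cent of schools: 9 schools, 3 per arm, 8.7 classes and 260 students per arm

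**The plan's own figure.** The 80% cannot be reproduced directly because no effect size is attached to it. The check is therefore which difference has 80% power on these inputs.

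**Formulas.** Design effect DE = 1 + (m − 1) × ICC. Effective number per arm = 260/DE. Detectable difference in SD = (z for two-sided alpha + 0.8416) × √(2/effective number).

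**Nine schools, ICC 0.2 at class level.**
- DE = 1 + (29.9 − 1) × 0.2 = 6.78
- Effective number per arm = 260/6.78 = 38.4
- √(2/38.4) = 0.228
- Alpha 0.05: (1.960 + 0.8416) × 0.228 = 0.64 SD
- Alpha 0.025: (2.241 + 0.8416) × 0.228 = 0.70 SD

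Power at given differences under this reading:

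| Difference (SD) | Alpha 0.05 | Alpha 0.025 |
|---|---|---|
| 0.30 | 26% | 18% |
| 0.35 | 33% | 24% |
| 0.50 | 59% | 48% |

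One-sided testing at 0.05 still gives 0.57 SD.

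**What would bring it down to 0.5 SD.** Adjusting for baseline multiplies the detectable difference by √(1 − r²), so r = √(1 − (0.5/0.64)²) = 0.62 at alpha 0.05, and √(1 − (0.5/0.704)²) = 0.70 at alpha 0.025. This also needs school-level variance to be negligible.

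**Sensitivity: ICC 0.2 at school level.** DE = 1 + (86.7 − 1) × 0.2 = 18.1 and the effective number is 14.3 per arm. The detectable difference is 1.05 SD (alpha 0.05) or 1.15 SD (alpha 0.025).

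**Sensitivity: 780 students spread over many more clusters.** The second row keeps 80% of schools, the follow-up fraction that the article assumes for the primary outcome.

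| Spread | Students per cluster | DE | Effective number per arm | Alpha 0.05 | Alpha 0.025 |
|---|---|---|---|---|---|
| All 261 classes, class ICC | 3.0 | 1.40 | 186 | 0.29 SD | 0.32 SD |
| 72 schools, school ICC | 10.8 | 2.97 | 87.6 | 0.42 SD | 0.47 SD |

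**Sampling unit.** To obtain 780 students from 9 schools, each school must supply 780/9 = 86.7, which is the whole average number per school in the trial's total. That fits poorly with a convenience sample that depends on parental consent.

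**The case against.** Four points can be made for the plan.

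*The two sections are compatible.* A reader might infer that they contradict each other. The documents do not support that: at 86.7 students per school, 10% of schools is also 10% of the students. The list of strengths and limitations and the Discussion both say that only a subset of schools provides student data, which favours the nine-school reading. No section describes 780 students spread over all classes. What stands is that the sampling unit is unclear, because nine schools would need almost complete consent.

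*Baseline data exist.* Fitness is measured in weeks 1 and 8 and mixed models are planned, so adjustment is possible. With r = 0.7 the detectable difference falls to 0.46 SD (alpha 0.05) or 0.50 SD (alpha 0.025), the upper edge of a small-to-moderate range. It would therefore be wrong to say that the power claim can hold only if students are spread across all schools. But the article states no such correlation, and the claim as printed does not rest on one.

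*The effect size is not numerical.* This is so, and the statement is unsupported rather than proven false. Still, no two-sided or one-sided variant tried on the stated inputs for nine schools reaches 80% power at 0.5 SD or less.

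*The outcomes are secondary.* This also stands. The primary reach calculation is not in question: with a difference of 12.5 percentage points, SD 12 and alpha 0.025, 24 of 30 schools per arm give 91% power.

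**Conclusion.** The concern holds for the stated figure. With nine schools and ICC 0.2 at class level, 80% power is reached at about 0.64 SD (alpha 0.05) or 0.70 SD (alpha 0.025), and power for 0.5 SD is 59% or 48%. This rests on equal arms, average cluster sizes, normal critical values, no baseline adjustment and no extra school-level variance. Apart from the missing baseline adjustment, these assumptions favour the plan.

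A reader might go further and take differences above 1 SD as the plan's true detectable effect. Those figures put the correlation at school level, whereas the analysis adjusts for class and expects little school-level clustering beyond it, so they are only a sensitivity case. Nor does the article say that a null student result will be read as equivalence; that is a risk of the wording, not a stated intention. The point should be fixed, but it touches secondary outcomes only.

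**What to change.** Use one sampling basis in the Sample size calculation and Impact evaluation sections, with the expected schools, classes and students per arm. Replace the 80% power statement with the detectable difference that follows from that basis, and state the level of the ICC and the alpha.

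- If nine schools are meant, give about 0.64 to 0.70 SD unadjusted, or the adjusted value with the assumed baseline correlation stated. Unless that adjusted value supports it, do not present the student comparisons as powered for small-to-moderate effects.
- If 780 students from many more schools are meant, say so and give the matching figure, about 0.3 to 0.47 SD depending on the spread, the level of the ICC and the alpha.

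The cost is rewording two passages. On the nine-school basis the stated power becomes less favourable. No extra students are needed, and the primary analysis is unchanged.

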### Blinding and randomisation

After teachers have completed the RT4T workshop, schools will be randomised to one of three implementation support arms. Schools will be stratified by school type, socioeconomic status and location and randomised using a random number producing algorithm by an independent statistical analysis service. Data analysis will be conducted by individuals blinded to group allocation.

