### School recruitment and selection

Secondary schools (government, Catholic and independent) in five local health districts in NSW (Illawarra Shoalhaven, Northern NSW, South Eastern Sydney, Sydney and Western NSW) will be eligible to participate in this study. Schools outside these districts will be able to attend the professional learning workshops and implement RT4T, but will not be included in the study to assess implementation outcomes. Eligible schools will be those that include students in grades 9 and 10 (aged 14–16 years). We will use a range of evidence-based recruitment and retention strategies to maximise participation and minimise dropout (at both school and teacher levels), including promotion within the NSW Department of Education School Sport Unit newsletter. This will include prenotification, the use of a dedicated recruitment coordinator, repeated reminders and deployment of staff from local health promotion teams to engage with schools.

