#### Professional learning for teachers

The school champion will complete a 30 min online course prior to programme delivery. This will include modules covering foundational principles of RT and specific safety recommendations to deliver RT to school-aged youth. Following initial completion of the online learning, the school champion will attend a single full-day workshop covering the background/rationale, structure and implementation of the RT4T programme, delivered by members of the research team with relevant expertise in PE, health promotion, exercise physiology and strength and conditioning.

School champions will be asked to attend the professional learning workshop and deliver a compressed training module to other grade 9 and 10 teachers within their schools. The compressed module comprises a train-the-trainer approach that is supported by resources (ie, presentation slides) provided by the research team. Our goal is to enable all interested and eligible teachers to deliver the RT4T programme to maximise the reach of the RT4T programme across the eligible student population.

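### The school-level t-test for reach leaves out enrolment, the denominator of reach, and so may forgo precision that a covariate would recover at almost no cost

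*Protocol article*

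**What the plan says.** All references are to the Protocol article.

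- **Eligibility** (School recruitment and selection): "Secondary schools (government, Catholic and independent) in five local health districts in NSW" may join, and "Eligible schools will be those that include students in grades 9 and 10". No minimum or maximum enrolment is given.
- **Allocation** (Blinding and randomisation): "Schools will be stratified by school type, socioeconomic status and location and randomised using a random number producing algorithm". Size is not among the factors.
- **Primary outcome** (Primary and secondary outcomes): students attending at least half of the practical sessions, "divided by the total number of students in grades 9 and 10 at the study schools".
- **Analysis** (Statistical analysis): "The primary outcome (ie, reach) will be collected at the school level and assessed using t-tests". No covariate is named. The same section opens with a general sentence that assigns primary and secondary outcomes to mixed models, but the sentence specific to reach names the t-test.
- **Delivery input** (Teachers): "One or two teachers from each enrolled school who teach students in grades 9 and 10 will be recruited" as champions. About 100 exercise cards go to each school (Materials and equipment). High-support schools get one equipment pack each (Table 1). None of this is scaled to size.
- **Delivery by others**: champions train further grade 9 and 10 teachers, "who also have the option to implement the programme with their classes" (Teachers), and "Our goal is to enable all interested and eligible teachers to deliver the RT4T programme" (Professional learning for teachers).

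**The concern.** Two schools that deliver the same number of classes can have very different reach because their enrolments differ. Two classes of 30 give 60/60 = 100% in a school with 60 eligible students and 60/400 = 15% in one with 400. Delivery by teachers other than the champions is optional, so it is plausible that the numerator does not keep pace with the denominator.

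If so, part of the between-school spread in reach reflects enrolment and has nothing to do with support level. An unadjusted t-test leaves that spread in the error term. Enrolment is settled before randomisation and has to be obtained anyway for the denominator, so the loss would be avoidable. The plan has little slack to absorb it, and the Sample size calculation section itself says that there was little information to guide the power calculation.

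A second, smaller matter is reporting. The outcome is worded as a proportion of students across the study schools, whereas a t-test on school values weights every school equally. The two summaries differ when reach varies with size.

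**Working it through.** **1. The plan's own figure.** Inputs from Sample size calculation: difference 25 - 12.5 = 12.5 points, SD 12, alpha 0.025 (taken as two-sided; the text does not say), power 90%, 30 schools per arm, 20% lost, so 30 × 0.8 = 24 analysed per arm.

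- Normal approximation: n = 2 × (2.241 + 1.282)² × 12² / 12.5² = 22.9, so 23 per arm. 23/0.8 = 28.75, so 29 against the stated 30.
- Power at 24 per arm: standard error = 12 × √(2/24) = 3.46; non-centrality = 12.5/3.46 = 3.61; 46 degrees of freedom. Power is 91.4% (normal) or 89.8% (exact t).

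The stated figure reproduces. For 90% by exact t at 24 per arm, the SD must be 11.95 or less.

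**2. How much variance could enrolment explain?** The documents give neither a size distribution nor a link between size and delivery, so these inputs are assumptions: lognormal enrolment with mean 300 and coefficient of variation (CV) 0.4, 0.6 or 0.8, clipped to 30-900; 30 students per class (the plan gives 7800/261 = 29.9); number of delivering classes Poisson with mean λ × (enrolment/300)^e; students reached = the smaller of 30 × classes and enrolment. The exponent e sets how far delivery scales with size. λ = 3 is close to the plan's 261/90 = 2.9 classes per school and gives pooled reach of about 29-30%. λ = 1.25 gives about 12.5%, the planned low-arm value.

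Share of variance in school reach explained by log enrolment (CV 0.4 / 0.6 / 0.8):

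| Scaling of classes with size | λ = 3 | λ = 1.25 |
|---|---|---|
| None (e = 0) | 27 / 40 / 48% | 14 / 22 / 28% |
| Square root (e = 0.5) | 8 / 13 / 16% | 4 / 6 / 8% |
| Full (e = 1) | 0% | 0% |

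**3. What adjustment would buy.** Residual SD = 12 × √(1 - R²), with 24 per arm and two-sided 0.025. The reduction in standard error is 1 - √(1 - R²).

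| R² | Residual SD | Reduction in SE | Exact-t power |
|---|---|---|---|
| 0% | 12.0 | 0% | 89.8% |
| 4% | 11.8 | 2% | 91.0% |
| 8% | 11.5 | 4% | 92.2% |
| 16% | 11.0 | 8% | 94.4% |
| 27% | 10.3 | 15% | 96.9% |

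The degree of freedom spent on the covariate (45 instead of 46) changes these powers by less than 0.1 point. With R² = 0, power goes from 89.8% to 89.7%.

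**4. Chance imbalance.** The SD of the shift in the arm difference due to size is 12 × √R² × √(2/24). This is 0.7 points at 4% and 1.4 at 16%, against a target difference of 12.5.

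**5. Equal-weight versus pooled reach.** With no scaling and λ = 3, mean school reach is 34 / 38 / 42%, against pooled student reach of 30 / 29 / 29%. With full scaling the two agree.

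**The case against.** The strongest case against runs as follows.

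- **Only the denominator depends on size by construction.** Train-the-trainer lets the numerator grow with the school, all materials are also on a website, and the programme is designed to need little equipment. This stands. A reader might infer that reach must fall as enrolment rises; the documents do not establish that, and with full scaling the gain is zero.
- **The assumed inputs do not match the planned figures.** This also stands in part. With no scaling, the simulated SD of reach is 15-31 points against the planned 12, so the upper end of the R² range should not be read as a forecast. At the planned low-arm reach the shares are roughly half those at λ = 3.
- **The SD of 12 may already contain size variation.** It may. A reader might infer that the trial is underpowered, but the stated power reproduces and no stated figure is shown to be wrong.
- **Chance imbalance is not bias.** Correct. Randomisation protects the comparison, and the t-test's standard error already allows for such imbalance, so type I error is not inflated.
- **Leaving size out of the stratification is defensible.** Agreed. With three school types and two levels each of socioeconomic status and location (the last two assumed), there are 12 cells and 90/12 = 7.5 schools per cell across three arms. A fourth two-level factor would leave 3.75. Stratifying would also not by itself reduce the error variance of an unadjusted t-test.
- **Covariates belong in an analysis plan that is not shown.** This does not fully answer the point. The article does not leave the method open: it names a t-test, which has no place for a covariate.

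**Conclusion.** The concern holds as a point about efficiency. The named primary test ignores a baseline variable that is the outcome's own denominator, is unrestricted by eligibility and is not used in allocation. If delivery grows less than proportionally with school size, which is plausible but not shown, the plan gives up precision. With square-root scaling the standard error would fall by about 2-8% and power would rise from 89.8% to about 91-94%. With no scaling the gain is larger, and with full scaling there is none.

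The range rests on an assumed size distribution, assumed delivery models and the planned SD of 12 with 24 schools per arm. The documents do not support the stronger conclusions that the comparison is biased, that the sample size is wrong, that size is the dominant source of variation, or that the stratification is faulty.

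**What to change.** In Statistical analysis, replace the t-tests for reach with a school-level linear model (or equivalent) of reach on arm. Include log baseline grade 9 and 10 enrolment, with its value fixed at randomisation, as a pre-specified covariate. Keep the stated contrasts and significance thresholds.

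Report enrolment-weighted reach by arm beside the unweighted mean of school values, and say which one the test addresses, because the outcome definition is worded in terms of students.

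No change to the stratification is needed. The cost is a change of wording and one degree of freedom. The only data needed are the baseline enrolment counts, a quantity that the trial must obtain anyway to calculate reach. If size proves irrelevant, almost nothing is lost.
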